### Follow-up

After randomization, the patients will be followed every 3 months, or more often if the patient’s situation requires it, for at least 2 years. Patients in this study will undergo plain/enhanced computed tomography every 3 months to assess postoperative recurrence and metastases. Patients with iodine allergies will undergo plain computed tomography plus enhanced magnetic resonance imaging. The accuracy of the latter study method is not inferior to that of the former [21, 22]. RFS is defined as the time from operation to the time of finding any recurrence or metastasis or until death. OS is defined as the time from operation to the time of the last follow-up or death.

### Data and safety monitoring

During the study, an independent data monitoring committee (Clinical Study Support Center, Wakayama Medical University) will monitor the safety of the trial subjects by qualitative analyses of feasibility, accrual rate, and adverse events, as well as dropouts every 6 months. Data are collected via a case report form using paper and stored and managed securely by the data monitoring committee. To improve the quality of data, after written consent is signed, all baseline assessments will be conducted before randomization. The handling of all cases is managed by subject identification code or anonymized registration number. The correspondence table of the anonymizing codes and names, as well as the consent form containing the name, is kept in separate restricted-access lockable document storage at each participating institution. To promote data quality, missing data will be pursued until received or confirmed as unavailable, or until the trial reaches analysis. No interim analyses are planned in the ISOP-DP trial. The principal investigator has the right to terminate the trial at any time in consultation with the biostatistician. The trial would be terminated if the incidence or severity of adverse events in the trial indicated a potential health hazard caused by the study treatment. The trial is terminated if patient enrollment appears unsatisfactory with respect to quality or quantity, if data recording is severely inaccurate or incomplete, or if external evidence renders it necessary. The procedure for deciding to discontinue the entire study is as follows: the principal investigator must request a review by the Wakayama Medical University Ethics Review Board and make a report. If the principal investigator decides to discontinue the entire research, the principal investigators of the other institutions will be immediately notified of the reason and subsequent actions. The principal investigator of the other institutions contacted informs the subjects of the discontinuation of the entire research and the reason and takes appropriate action immediately. All adverse events observed by the investigators will be recorded up to 90 days after surgery and reported to the principal investigator and clinical trial coordination center. The assignment of the severity or grading should be made by the investigator responsible for the care of the participant. Serious adverse events are defined as those that are life-threatening or result in death. Serious adverse events will be collected and recorded according to good clinical practice throughout the study period. The patients enrolled in this study will receive standard-of-care supportive measures and all other medically necessary interventions as needed.

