## Methods/design

### Study design and overview

The ISOP-DP trial is a Japanese multicenter, randomized, controlled trial. Patients with PDAC are randomized to arm A (conventional procedure) or arm B (isolation procedure) during DPS. The ISOP-DP trial is conducted in 11 Japanese high-volume centers (Additional file 1, institution list) that have been board-certified as training institutions by the Japanese Society of Hepato-Biliary-Pancreatic Surgery. To ensure the high quality of the study, interventions are performed by instructors and expert surgeons certified by the society. This study aims to evaluate the oncological and surgical benefits of the isolation procedure during DPS for patients with PDAC in comparison with the conventional procedure. This study is therefore designed to evaluate the superiority of the isolation procedure (arm B) compared with the conventional procedure (arm A) during DPS in terms of a 2-year recurrence-free survival (RFS) rate. All patients are required to undergo postoperative examination every 3 months for at least 2 years after surgery. Signs of suspected disease recurrence will be closely monitored. The schedule of this trial is shown in Fig. 1. The study period of the ISOP-DP trial is expected to be 4 years, including 2 years for patient recruitment and 2 years of follow-up.

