### Study endpoints

The primary endpoint is the 2-year RFS rate. Secondary endpoints include operative time, intraoperative blood loss volume, and transfusion; incidence of postoperative complications within 90 days after surgery (including grade B or C pancreatic fistula, delayed gastric emptying (DGE), and intra-abdominal hemorrhage); all-morbidity rate within 90 days after surgery; and mortality rate within 90 days after surgery. We also include the rates of R0 and R1, number of harvested lymph nodes, number of metastatic lymph nodes, lymph node ratio, overall survival (OS) time, RFS time, and local recurrence rate. R0 status is defined as the absence of tumor cell infiltration within 1 mm of the resection margin, and R1 status is defined as the presence of tumor cell infiltration within 1 mm of the resection margin [13]. Postoperative pancreatic fistula (POPF) [14], DGE [15], and intra-abdominal hemorrhage [16] are defined and graded according to the International Study Group of Pancreatic Surgery (ISGPS) criteria. Postoperative complications other than POPF, DGE, and intra-abdominal hemorrhage are graded by the Clavien-Dindo classification [17]. Postoperative diarrhea is graded according to the Common Terminology Criteria for Adverse Events version 4.

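### After day 90 only life-threatening or fatal events are collected, so other late surgical complications that need readmission or reoperation meet no stated recording rule

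*Protocol article*

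**What the plan says.** Three rules stand close together in the protocol article under Data and safety monitoring:

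- General recording window: "All adverse events observed by the investigators will be recorded up to 90 days after surgery".
- Definition of serious: "Serious adverse events are defined as those that are life-threatening or result in death".
- Recording window for serious events: "Serious adverse events will be collected and recorded according to good clinical practice throughout the study period".

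Study endpoints sets the safety outcomes on the 90-day window as well: "incidence of postoperative complications within 90 days after surgery", "all-morbidity rate within 90 days after surgery", and mortality over the same period. Pancreatic fistula, delayed gastric emptying and intra-abdominal hemorrhage are graded by ISGPS criteria, and for the rest "Postoperative complications other than POPF, DGE, and intra-abdominal hemorrhage are graded by the Clavien-Dindo classification".

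Patients stay under observation much longer. Study design and overview says that "All patients are required to undergo postoperative examination every 3 months for at least 2 years after surgery". The monitoring committee is to "monitor the safety of the trial subjects by qualitative analyses of feasibility, accrual rate, and adverse events", at 6-monthly intervals.

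**The concern.** The word serious carries a practical consequence in this plan: after day 90 it alone decides whether an event is written down. With only two criteria, a patient who is readmitted or reoperated on in month 5 for a complication of the pancreatectomy, without danger to life, has had an event that no stated rule captures.

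At stake is the description of late surgical harm in a trial of two surgical procedures. The Discussion says that a finding of no significant differences would support both procedures on surgical as well as oncological grounds. As the recording rules stand, the surgical part of that statement would rest on the first 90 days plus late events that killed or threatened life. Events never recorded cannot be recovered by changing the definition at analysis.

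**Working it through.** No design figure is involved, and sample size, power and type I error do not depend on this point. The check is a comparison of the rules, with simple arithmetic for the time covered.

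**Inputs**
- General recording window: 90 days after surgery (Data and safety monitoring).
- Serious-event window: the whole study period (same section).
- Serious criteria: life-threatening, or fatal (same section). No other section adds a criterion.
- Complication, morbidity and mortality endpoints: 90 days (Study endpoints).
- Minimum follow-up: 2 years, taken as 2 × 365 = 730 days, with 3-monthly examinations (Study design and overview; Follow-up).

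**Which events are recorded, by period**

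| Event | To day 90 | After day 90 |
|---|---|---|
| Fatal or life-threatening | Recorded, serious | Recorded, serious |
| Readmission, reoperation or prolonged stay, not life-threatening | Recorded and graded, not labelled serious | No stated recording rule |
| Recurrence or death | Captured by RFS and OS | Captured by RFS and OS |

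Only the second row has a gap, and only in its last column.

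**Length of the gap**
- 730 − 90 = 640 days.
- 640 / 730 = 0.877, so about 88% of the minimum follow-up. The full recording rule covers 90 / 730 = 0.123, about 12%.

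**Does another rule close it?**
- The endpoints do not, because they also stop at 90 days.
- The 3-monthly visits do not as described. The Follow-up section gives their content as imaging for recurrence and metastasis.
- The reference to good clinical practice does not. It governs how serious events are collected, while the sentence before it has already fixed which events are serious.

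**Number of events in the gap**
The documents give no complication rate and no rate of events after day 90, so no count or range can be derived from them.

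**The case against.** The strongest case against is that the plan already handles the harms that matter. Fistula, delayed gastric emptying, hemorrhage and overall morbidity are secondary endpoints to day 90. They are graded, and the analysis plan section compares categorical outcomes between arms with Fisher's exact test. A 90-day limit for surgical complications is a legitimate design choice, and the plan promises no later comparison. Late deaths and recurrences are counted through OS and RFS. The article also condenses a fuller protocol that may define serious events more widely.

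Most of this stands, and it narrows the point to the period after day 90. It does not remove the point. The plan chooses to keep collecting serious events throughout the study, so the definition determines what that collection contains. The article does not leave the definition to another document: it states a complete one. If the full protocol is wider, the article misreports it.

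Two stronger readings are tempting and are not supported.

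- A reader might infer that the monitoring committee and the termination rule would work from an under-count. Neither is tied to the serious label: both refer to adverse events in general, and to day 90 all of these are recorded. Beyond day 90 they can draw only on what is recorded, which is the same gap and not a further one.
- A reader might assume that 10–30% of the 100 patients have a complication that prolongs stay or needs reintervention without threatening life, and count 10–30 events as lost. That rate is not in the documents and is not split at day 90. Any such event up to day 90 is recorded, so the figure would mostly describe labelling.

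**Conclusion.** The point holds in a limited form. For about 640 of the 730 days of minimum follow-up, non-fatal and non-life-threatening complications of surgery that lead to readmission or reoperation fall outside every recording rule that the article states. Up to day 90 the only effect is that such events are not called serious.

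The primary endpoint, the 90-day endpoints, and the termination rule as worded are untouched. The conclusion rests on reading the article's definition as complete, which its wording supports, and on the absence of any other late recording rule in the document. It does not rest on an assumed event rate, and the number of events missed may be few. This is a safety-recording weakness that is worth correcting because the correction is cheap, and because late events cannot be recovered once they go unrecorded.

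**What to change.** Reconcile the definition of a serious adverse event with the section's own reference to good clinical practice. In addition to fatal and life-threatening events, include those that require or prolong hospitalization (including for reoperation or reintervention), cause persistent disability, or are otherwise medically important.

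State an exclusion for admissions due solely to disease recurrence or its planned treatment. Without it the reports would be swamped. The recurrence figures quoted under Sample size, 75% and 67% over about 2 years, would mean roughly 0.75 × 50 + 0.67 × 50 = 37.5 + 33.5 = 71 patients with recurrence among the 100 if they applied here, and RFS and OS already capture that outcome.

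Collect the added events at the existing 3-monthly visits, and tabulate them by arm in the committee's 6-monthly review.

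The cost is a change of protocol wording, some additional serious-event forms, and a judgement for each late admission on whether recurrence was the sole cause. No extra visits are needed, and neither the sample size nor the primary analysis changes.

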
### Ethics

#### Research ethics approval

This study is performed in accordance with the Declaration of Helsinki. The protocol has been approved by the Wakayama Medical University Hospital Ethics Committee (approval number 2986). The trial protocol has also been registered in the protocol registration system at ClinicalTrials.gov (NCT) and the University Hospital Medical Information Network Clinical Trials Registry (UMIN). All patients will be scheduled only after comprehensive information concerning the nature, scope, and possible consequences of the clinical trial have been provided to them in an understandable way by the investigator. Written informed consent to inclusion in the study will be obtained from each patient before the operation. The procedure, benefits, risks, and data management of this study will be clarified in detail for the patients during the preoperative conversation.

#### Dissemination policy

The results of the ISOP-DP trial will be submitted to a peer-reviewed journal and will be presented at national and international conferences, regardless of the trial outcomes. Authorship will be agreed in accordance with the ISOP-DP trial publication policy and in line with international guidelines.

## Discussion

The oncological impact of the isolation by the so-called non-touch technique remains controversial in digestive surgery [1–4, 23]. The outcome could be affected by anatomical features of vessels connected to organs in which cancer has developed, or by minimal invasiveness of manipulation with laparoscopic/robotic forceps. Although Strasberg et al. may have intended to report the RAMPS procedure with focus on the number of lymph nodes dissected and the higher R0 resection rate, this procedure also has potential as an isolation procedure for the pancreato-splenic area by division of the splenic vessels and transection of the pancreas in the early stages of surgery. The RAMPS procedure has been reported to demonstrate a significantly higher R0 resection rate and a higher number of lymph node dissections than standard DP [5, 6]. Meanwhile, in a recent systematic review and meta-analysis, there were no significant differences in recurrence rate, OS, or DFS [11]. In other systematic reviews and meta-analysis, the RAMPS procedure was shown to have better surgical outcomes (time and bleeding volume) and pathological outcomes with a significantly higher R0 resection rate and a larger number of lymph node dissections than the standard DP [12]. Otherwise, there were no significant differences in postoperative pancreatic fistula, postoperative complications, length of stay, or mortality. There was no significant difference in the postoperative recurrence rate, but the only finding of favorable survival outcome was 1-year postoperative OS with the RAMPS procedure. Surprisingly, in these systematic reviews and meta-analysis, all studies analyzed were retrospective, and many of them were historically controlled studies in which surgery was performed by the RAMPS method in recent years when surgical techniques and devices were developed. The most important endpoint in the treatment of pancreatic cancer is OS, although what exactly contributes to the extension of OS in RAMPS procedures is unclear and remains controversial.

In an international multicenter study, Korrel et al. reported that Gerota’s fascia resection, R0 resection, and reduction in LNR were factors associated with improved overall survival in DP-treated PDAC [24, 25], but the surgical approach was not included as a risk factor in their analysis. There is a possibility that the squeezing out of tumor cells can be reduced by a surgical approach. It has become possible in recent years to observe and manipulate the deep abdominal cavity and the retroperitoneal space in detail with a laparoscopic field of view and developed surgical devices. As a result, the oncological impact of the isolation technique may be greater than the difference in the direction of the retroperitoneal dissection. If there is an oncological benefit in the RAMPS procedure, it may be due to early blockage of the lymphatic, arterial, and portal venous system in the pancreatic body/tail by prioritizing the vascular dissection in the excision phase. However, the oncological benefits of this surgical procedure have not yet been demonstrated in prospective randomized controlled trials.

If the ISOP-DP trial shows that the isolation procedure can improve recurrence-free survival with a similar R0 rate and a similar number of lymph node dissections to the conventional procedure, the isolation procedure is expected to become a worldwide standard procedure during DPS for PDAC under the concept of isolation technique. Otherwise, if there are no significant differences in endpoints between the groups, it will demonstrate that both procedures may be justified from surgical and oncological points of view.

## Trial status

The ISOP-DP trial was opened in October 2020. At the time of submission of this paper (January 2021), the protocol is version 1.0. The completion date is estimated to be September 2025.

## Data Availability

The datasets used and/or analyzed will be available from the corresponding author on reasonable request after the current study is complete.

## Abbreviations

RAMPS: Radical antegrade modular pancreatosplenectomy
PDAC: Pancreatic ductal adenocarcinoma
INDICE cloud: UMIN Internet Data and Information system for Clinical and Epidemiological research, cloud version
NCCN: National Comprehensive Cancer Network
OS: Overall survival
DPS: Distal pancreatosplenectomy
POPF: Postoperative pancreatic fistula
DGE: Delayed gastric emptying
PV: Portal vein
SMA: Superior mesenteric artery
SMV: Superior mesenteric vein
